### Primary efficacy study parameter

The primary endpoint is the composite of the incidence of all TEC, including myocardial infarction, leg ischemia, deep venous thrombosis, colon ischemia, stroke, graft thrombosis, thrombo-embolic complications in the kidney or spleen and other peripheral thromboses and all-cause mortality within 30 days after surgery or during the same admission, and peroperative thrombosis requiring additional actions peroperatively (i.e., embolectomy, atherectomy, or re-do of an anastomosis because of thrombus). The statistical efficacy analysis will be conducted with a chi-square test for proportions. Differences in the incidence of this composite endpoint between the intervention and control groups will be expressed as the absolute risk difference with a 95% confidence interval.

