### Sample size calculation {14}

In the DSAA (2014 to 2016), the rate of serious complications was 29% for all patients. According to the Society for Vascular Surgery AAA 2018 guidelines, the incidence of TEC is between 15 and 36%. In our preliminary MANCO trial, the incidence of TEC was 14%. For our power calculation, the incidence of TEC is set at 14%. The vast majority of mortality after open AAA repair stems from TEC. A mortality rate of 5% after open AAA repair is derived from DSAA. The hypothesis is that a decrease of TEC will result in a lower mortality of 3%. Bleeding complications derived from the literature and from our MANCO trial and ACTION pilot study are 18–39% (scored according to E-CABG classification) [30].

Derived from data from our pilot study and from literature, the hypothesis is that ACT-guided heparinization will lower the rate of TEC to 8%. The expected incidence for the combined endpoint of TEC and mortality is therefore set at 19% for the 5000 IU group and 11% for the ACT-guided group. Using a continuity corrected chi-square test with a two-sided alpha of 5%, 337 patients are needed in each group to achieve a power of 80%. Including a dropout of 10%, a total of 750 patients are needed for the combined primary endpoints of TEC and mortality.

In our pilot study, no increase in bleeding complications was found for open AAA repair (E-CABG class 1 bleeding was 39% versus 36%). Nevertheless, it is important that excessive bleeding does not occur in the intervention group. Therefore, a non-inferiority calculation was performed. Bleeding complications and TEC are different and have a different impact on patients. Bleeding complications grade 1 E-CABG have less impact on mortality and quality of life than TEC. The expectation is an improvement in combined TEC and mortality of 8%, and the non-inferiority for bleeding complications is set at 11%.

Expecting 32% bleeding complications in the standard group and 33% in the intervention group and a non-inferiority limit of 43% (11% limit difference) with a power of 80% and a one-sided alpha of 5%, 272 patients are required in each group. Therefore, the 750 patients which are needed for the combined primary endpoints of TEC and mortality are sufficient to also evaluate the non-inferiority for bleeding complications.

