### Randomization {16 a,b,c}

Randomization will take place just before the start of surgery by one of the researchers of the sponsor, who is present in the operating room during the entire procedure. A computerized program (CASTOR EDC) is used with a random block size of 2, 4, and 6. The randomization will be stratified by participating center. The assigned group (ACT or 5000 IU) is displayed on the computer, immediately after randomization. The researcher will inform the anesthesiologist which dose of heparin should be administered.

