### Primary safety study parameter

Incidence of bleeding complications according to E-CABG classification, grade 1 and higher [31]. For the bleeding complications, a non-inferiority test will be used. We test the hypothesis that the difference in bleeding between the intervention group and the control group is below the a priori specified boundary of 11%. This will be tested using a one-sided *t* test with an alpha of 0.025, with the null hypothesis that the number of bleedings is above the threshold margin and the alternative hypothesis that is below the threshold margin. If the confidence interval for the bleeding complications does not include the non-inferiority limit in the per-protocol analysis and in the intention-to-treat analysis, non-inferiority for bleeding complications is established.

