## Discussion

The ACTION-1 trial is conducted to investigate if ACT-guided heparinization might lead to better (patient related) outcomes than a standardized bolus of 5000 IU of heparin without measuring its effect. The trial will be executed during open AAA repair in 18 large Dutch Vascular Centers (University and non-University) and 2 major centers in Germany and Denmark.

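### Randomisation is stratified by centre but both primary tests ignore centre; if event rates differ between centres, the tests are somewhat conservative and a little efficiency is lost

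*Protocol article*

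**What the plan says.** Under Randomization, "The randomization will be stratified by participating center"; centre is the only factor named. The allocation program "is used with a random block size of 2, 4, and 6". The Discussion expects "18 large Dutch Vascular Centers (University and non-University) and 2 major centers in Germany and Denmark", so about 20 strata.

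For the primary composite, the section on the primary efficacy study parameter states: "The statistical efficacy analysis will be conducted with a chi-square test for proportions". The difference "will be expressed as the absolute risk difference with a 95% confidence interval". The section on the main efficacy endpoint names the same test.

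For bleeding, the section on the primary safety study parameter states: "This will be tested using a one-sided *t* test with an alpha of 0.025", against an 11% margin, to be met in both the intention-to-treat and the per-protocol analysis.

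Centre enters neither primary analysis. Under Other study parameters, hospital appears only in side analyses: each hospital's first five patients against later ones, and the effect of its earlier heparin protocol.

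**The concern.** Small blocks within centre keep the two arms nearly equal in every hospital, so a hospital with a high or low event rate contributes to both arms alike. The design has removed that source of variation from the comparison, but the named tests compute their standard errors as if it were still there. When rates differ between hospitals, the interval is wider than it need be and the test rejects less often than its nominal level.

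Such differences are plausible here. Postoperative treatment follows each hospital's own protocols (Follow-up and quality of life measurements), and grade 1 bleeding is largely defined by transfusion of red cells, platelets or plasma (Main study parameter/endpoint safety), which depends partly on local practice. At stake is a modest amount of power and interval width that could be had without extra patients.

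**Working it through.** **Inputs from the protocol.** Composite "set at 19% for the 5000 IU group and 11% for the ACT-guided group"; two-sided alpha 5%; 337 per group; bleeding 32% v 33%; margin 11 points; bleeding test at one-sided 0.025; blocks of 2, 4 and 6; about 20 centres. **Assumed, because the protocol does not give it:** the between-centre spread of event rates and the unequal centre sizes.

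**1. The plan's own figures reproduce.**
- Efficacy without continuity correction: n = [1.96·√(2·0.15·0.85) + 0.8416·√(0.19·0.81 + 0.11·0.89)]² / 0.08² = 311.6, so 312. With the correction: (311.6/4)·[1 + √(1 + 4/(311.6·0.08))]² = 336.1, so **337**. With 10% dropout: 337/0.9 = 374.4, so 375 per arm and **750** in total.
- Bleeding at one-sided 5%: (1.645 + 0.8416)²·(0.32·0.68 + 0.33·0.67)/(0.11 − 0.01)² = 6.183·0.4387/0.01 = 271.2, so **272**.

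**2. Why the unstratified standard error is larger.** With centre rates p_k, patient shares w_k and overall rate p̄,

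p̄(1 − p̄) = Σ w_k p_k(1 − p_k) + Σ w_k (p_k − p̄)².

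The last term, τ², is counted by the unstratified test but cancels in the blocked comparison. The stratified-to-unstratified variance ratio is therefore about 1 − τ²/[p̄(1 − p̄)].
- Bleeding, p̄ = 0.325, p̄(1 − p̄) = 0.2194: τ of 5, 10 and 15 points gives 0.989, 0.954 and 0.897.
- Composite, p̄ = 0.15, p̄(1 − p̄) = 0.1275: τ of 3, 5 and 8 points gives 0.993, 0.980 and 0.950.

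A simulation with Beta-distributed centre rates (8,000 runs, 20 unequal centres, 337 per arm) gave 0.990, 0.957, 0.904 and 0.993, 0.982, 0.954, in agreement.

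**3. Effect on power.** A second simulation used 4,000 trials per scenario, N = 674, 20 unequal centres, blocks of 2/4/6 and a normal centre effect on the logit scale. It compared the uncorrected chi-square with the Cochran-Mantel-Haenszel (CMH) test. For bleeding it compared the unstratified Wald limit (standing in for the t test) with the Mantel-Haenszel limit (Sato variance), both with z = 1.96.

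| Logit SD | SE excess, efficacy | SE excess, bleeding | Efficacy power, chi-square → CMH | Non-inferiority power, unstratified → stratified |
|---|---|---|---|---|
| 0 | 0% | 0% | 82.8 → 82.5 | 78.8 → 78.7 |
| 0.25 | 0.3% | 0.6% | 83.2 → 83.2 | 78.5 → 79.3 |
| 0.5 | 1.3% | 2.3% | 83.8 → 84.2 | 79.2 → 80.6 |
| 0.75 | 3.1% | 5.0% | 83.8 → 85.1 | 79.8 → 83.1 |
| 1.0 | 5.4% | 8.4% | 83.4 → 86.0 | 81.6 → 86.3 |

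For scale, take 32% as the typical centre, logit −0.754. An SD of 0.5 puts 95% of centres between expit(−1.734) = 15% and expit(0.226) = 56%. An SD of 1.0 puts them between expit(−2.714) = 6% and expit(1.206) = 77%. The bottom row is an extreme.

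**4. Error rates.** Under a 15% v 15% null, SDs 0 to 1.0 in order, chi-square rejected in 4.70, 5.32, 4.05, 4.48 and 4.05% and CMH in 4.68, 5.40, 4.30, 5.35 and 4.88% (Monte Carlo error about 0.35 points). At the non-inferiority boundary (32% v 43%), the unstratified limit passed in 2.42, 2.08, 2.00, 2.30 and 1.68% and the stratified one in 2.38, 2.13, 2.25, 3.00 and 3.00% (error √(0.025·0.975/4000) = 0.25 points).

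**5. A caution on the larger SDs.** Away from the null, a constant odds ratio gives each centre its own risk difference, and the centres were redrawn in every run. At 19% v 11% and SD 1.0, the empirical SD of the crude difference (0.0287) therefore exceeds both mean standard errors (0.0272 and 0.0257). The statement that the unstratified error is too large refers to the participating centres as given. Part of the bleeding gain in the last two rows goes with a rejection rate slightly above 2.5%.

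**The case against.** **Size.** The protocol gives no between-centre variation, and the Background says open repair was chosen because its care is standardised across European hospitals. With no heterogeneity nothing is gained. This stands: the point is conditional and its size is a range.

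**Precision of the estimate.** The crude risk difference varies about as much as the Mantel-Haenszel one (empirical SD 0.02604 v 0.02601 under the null at SD 1.0). This stands: what is lost lies in the test and the interval, not in the estimate.

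**Left to an analysis plan.** A separate plan could add centre. But the protocol names the tests, so this concerns what is fixed, not what is left out.

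Three stronger readings are tempting and are not supported:
- *The primary tests are invalid or anti-conservative.* Ignoring a stratification factor makes the test conservative. No bias arises in the intention-to-treat comparison.
- *Stratifying is needed to rescue non-inferiority power.* At one-sided 0.025 and 337 per arm, SE = √(0.4387/337) = 0.0361, and power is Φ(0.10/0.0361 − 1.96) = 79.1%. At the 375 per arm to be randomised it is 83.2%. The small shortfall at 337 arises because the calculation used one-sided 5% and the test uses 0.025, which is a separate matter. Efficacy has slack, at about 83% for the uncorrected test.
- *The per-protocol comparison is confounded by centre.* Its exclusions could upset balance within centres, but the Discussion deems such deviations infrequent and equal in both groups. Nothing says they cluster by hospital, and the simulations did not model them.

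**Conclusion.** The mismatch between design and analysis is real and conservative in direction. It is an efficiency weakness, not a validity error, and the sample sizes of 337 per group, 750 in total and 272 per group stand.

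Over assumed logit SDs of 0 to 1.0 at 337 per arm, the unstratified standard error exceeds the stratified one by about 0–5% for efficacy and 0–8% for bleeding. The power gain is about 0–3 and 0–5 points. At SD 0.5, the middle of the range, the gain is 0.5 points for efficacy and 1.4 for bleeding. The upper ends need very large differences between hospitals and should not be relied on. The conclusion rests on about 20 unequal centres, blocking as stated, and heterogeneity that the documents make plausible but do not quantify. The case for changing the plan is that the analysis would then follow the randomisation at almost no cost.

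**What to change.** - **Efficacy:** make the primary analysis the Cochran-Mantel-Haenszel test and the Mantel-Haenszel risk difference, both stratified by centre, with a two-sided 95% CI.
- **Bleeding:** replace the t test with the same centre-stratified risk difference. Compare the upper bound of its two-sided 95% CI with the 11-point margin, in both the intention-to-treat and the per-protocol set. State explicitly that this is one-sided alpha 0.025, as in the primary safety section, so that it cannot be read as a one-sided 95% limit.
- **Small centres:** fix a pooling rule before unblinding.
- **Sensitivity:** keep the crude chi-square and the crude risk differences as sensitivity analyses.

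The cost is wording in the two efficacy and two safety paragraphs. No extra patients or data are needed, and the risk-difference scale and margin stay the same. Trial status reports 90 of 750 patients included, so the change can be prespecified well before analysis. The plan names SPSS for all analyses; the team should confirm that it produces the stratified risk difference with its variance, or name another program.

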### Other study parameters {12}

#### Preoperative parameters

Patient demographics: sex, smoking history, body length and weight and body mass index, medical history (general, cardiac, pulmonary, diabetes, surgical), medication, all previous vascular interventions; blood pressure and pulse at the outpatient visit, ECG reports; diameter and anatomical classification of abdominal or iliac aneurysms; preoperative laboratory results: Hb, leucocytes, sodium, potassium, creatinine, eGFR, platelets; presence of impaired renal function (eGFR < 40 ml/min).

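### The primary efficacy test is valid and correctly sized but unadjusted; a pre-specified adjusted risk difference would probably gain a little precision from baseline data already collected

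*Protocol article*

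**What the plan says.** Two sections of the protocol article, Main study parameter/endpoint efficacy and Primary efficacy study parameter, fix the same analysis: "The statistical efficacy analysis will be conducted with a chi-square test for proportions", with the group difference "expressed as the absolute risk difference with a 95% confidence interval". Neither names a covariate, and neither does the Statistical analysis section.

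Under Preoperative parameters the trial records, besides sex, smoking and body size, "medical history (general, cardiac, pulmonary, diabetes, surgical), medication, all previous vascular interventions", and "preoperative laboratory results: Hb, leucocytes, sodium, potassium, creatinine, eGFR, platelets". The Randomization section stratifies by participating centre.

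The Sample size calculation has the composite "set at 19% for the 5000 IU group and 11% for the ACT-guided group". It plans with a continuity-corrected chi-square at a two-sided 5% level, under which "337 patients are needed in each group to achieve a power of 80" per cent. It then states: "Including a dropout of 10%, a total of 750 patients are needed".

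Three rules in the Statistical analysis section bear on the point. The bleeding comparison is confirmatory only if efficacy is significant. Patients with missing data drop out of the analysis concerned. All analyses are to be run in SPSS.

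**The concern.** The composite includes myocardial infarction, stroke, leg and colon ischaemia and all-cause death. Cardiac history, renal function, diabetes and earlier vascular interventions are plausible predictors of such events. A two-by-two comparison uses none of that information, nor the stratification factor.

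For a binary endpoint, a logistic model standardised over the trial population estimates the same marginal risk difference as the raw proportions, usually with a smaller variance. The trial has one efficacy test planned at 80% power, and the confirmatory status of the bleeding test depends on it. A small gain in precision therefore serves both primary conclusions. The protocol's Discussion also names the inclusion rate as a possible concern, so precision that needs no extra patients has practical value.

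**Working it through.** **Inputs from the Sample size calculation.** Risks 0.19 and 0.11, so the difference is d = 0.08 and the mean risk is 0.15. Two-sided alpha 5% (z = 1.960), power 80% (z = 0.842), 337 per group, 10% dropout, 750 in total.

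**Assumed input.** R², the share of outcome variance explained by the baseline variables. The article gives no value; 0.02 to 0.10 is used.

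**1. Reproduce the plan's figure.**

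- Uncorrected: n = [1.960·√(2·0.15·0.85) + 0.842·√(0.19·0.81 + 0.11·0.89)]² / 0.08² = (0.990 + 0.422)² / 0.0064 = 311.5, so 312.
- Continuity-corrected: (312/4)·[1 + √(1 + 4/(312·0.08))]² = 336.5, so 337.
- Dropout: 337/0.90 = 374.4, so 375 per group and 750 in total.

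The stated figures reproduce.

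**2. Power of the unadjusted test at 337 per group.** The standard error is √(0.255/337) = 0.02751 under the null and √(0.2518/337) = 0.02733 under the alternative.

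- Uncorrected: Φ[(0.08 − 1.960·0.02751)/0.02733] = Φ(0.954) = 83.0%.
- Corrected, subtracting 1/337 = 0.00297 from d: Φ(0.846) = 80.1%.

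**3. Effect of adjustment.** Approximate the variance of the risk difference as multiplied by (1 − R²). This is equivalent to 337/(1 − R²) patients per group.

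| Assumed R² | Equivalent n per group | Power, uncorrected | Power, corrected | 95% CI half-width (points) | Corrected n per group for 80% | Total, ÷ 0.90 |
|---|---|---|---|---|---|---|
| 0 | 337 | 83.0% | 80.1% | 5.36 | 337 | 749 |
| 0.02 | 344 | 83.7% | 81.0% | 5.30 | 331 | 736 |
| 0.05 | 355 | 84.9% | 82.2% | 5.22 | 321 | 714 |
| 0.10 | 374 | 86.7% | 84.4% | 5.08 | 304 | 676 |

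The gain is 0.7 to 3.7 points uncorrected and 0.9 to 4.3 points corrected. In patients it is worth 749 − 736 = 13 to 749 − 676 = 73.

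**4. What these R² values mean.** With a normally distributed risk score and 15% overall risk, AUCs of 0.636, 0.684 and 0.727 correspond to R² of 0.031, 0.060 and 0.096. An R² of 0.02 to 0.10 is therefore an AUC of about 0.61 to 0.73. Even fair discrimination explains little variance at this event rate.

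**5. Simulation.** Each setting had 337 per group at 19% against 11%. Logistic standardisation with an influence-function standard error was compared with the uncorrected chi-square.

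| AUC | Variance ratio | Power, chi-square | Power, adjusted |
|---|---|---|---|
| 0.64 | 0.97 | 84.2% | 85.5% |
| 0.68 | 0.95 | 84.1% | 86.1% |
| 0.73 | 0.91 | 84.4% | 87.5% |

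These are 4,000 trials per setting with one covariate. Further runs agree:

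- With three covariates at AUC 0.64, 0.70 and 0.75, the variance ratios were 0.98, 0.94 and 0.90.
- At AUC 0.75, power went from 83.2% to 87.2%. Another run gave 88.6%, which is more than a ratio of 0.90 explains, so it is not relied on.
- A set of 3,000 trials per setting gave ratios of about 0.98, 0.93 and 0.88 and gains of about 1, 3 and 5 points.
- Type I error of the adjusted test was 5.0–5.3% in one set and 4.8–5.7% in another, where the chi-square gave 4.7–5.7%.

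The one- and three-covariate simulations had no centre effects, so any gain from centre is not quantified here.

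**6. Room for covariates.** Expected events are 0.19·337 + 0.11·337 = 64 + 37 = 101. The Discussion names 18 + 2 = 20 centres. A separate term for each would use 19 parameters, so small centres need pooling.

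**The case against.** The strongest reply is that nothing here is wrong. The chi-square is valid, it matches the sizing method in kind, and it already targets the marginal risk difference that the alternative would estimate. That stands, and it limits the point to a recommendation.

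Four stronger readings are tempting, and the protocol article does not support them.

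- **Strong predictors are being ignored.** No section gives prognostic strength. The composite also includes deep venous thrombosis, graft thrombosis and intraoperative thrombus, for which these variables may say little. Exclusions such as eGFR below 30 ml/min and life expectancy under 2 years narrow the risk range. Age is not in the printed list of preoperative parameters. The gain could be one power point or less.
- **Chance imbalance biases the result.** Under randomisation, the unadjusted confidence interval and type I error already allow for it. Adjustment can reduce that variability; there is no bias to remove.
- **No analysis will use the covariates.** The statistical analysis plan is not shown, and the article allows a sensitivity analysis if indicated. Only the choice of primary test is open to comment.
- **Adjustment gains more, counted from 80%.** The article does not say whether the final chi-square carries the continuity correction. The correction alone is worth 83.0% − 80.1% = 2.9 points. Moving from a corrected test to an uncorrected adjusted one would mix the two gains.

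**Conclusion.** The point holds as an efficiency recommendation. The unadjusted chi-square is valid and correctly sized, but it leaves plausible baseline predictors and the stratification factor unused.

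If the covariates explain 2% to 10% of outcome variance, the variance of the risk difference falls by about 2% to 10%, and power at 337 per group rises by roughly 1 to 4 points. The confidence interval half-width shrinks from 5.36 points to between 5.30 and 5.08. This rests on an assumed predictive strength, on the plan's 19% and 11%, and on a covariate list fixed without sight of outcomes by group. A reader should not infer that the trial is underpowered by its own assumptions or that its primary result would be invalid.

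**What to change.** Before unblinding, change Main study parameter/endpoint efficacy and Primary efficacy study parameter as follows:

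1. Make the primary analysis a logistic model with treatment, centre (small centres pooled by a stated rule) and a short fixed list from the eCRF: cardiac history, eGFR, diabetes and previous vascular intervention, each with a written definition.
2. Standardise the model to the marginal absolute risk difference, with its 95% confidence interval, and test on that scale.
3. Keep the chi-square as a supporting analysis, and say whether it carries the continuity correction.
4. Keep N at 750. The assumed R² is not a basis for recruiting fewer patients.

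In Statistical analysis, state that missing baseline covariates are filled by simple imputation and do not exclude the patient; otherwise the present missing-data rule would cost the adjusted analysis patients. Allow software other than SPSS if the standardisation needs it.

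The cost is wording, agreement on the covariate list in advance and a little more programming. No new data are needed.
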